### Study design

This feasibility study will use a within-subjects, repeated measures design to assess changes in mood (symptoms of depression and anxiety), mental wellbeing, study skills, and student engagement and satisfaction. These data will be used to evaluate potential primary outcome measures and inform the sample size for a future RCT. Figure 1 provides an overview of the study procedure. Ethical approval covering all sites was granted by Kings College London (KCL) College Research Ethics Committee (CREC), Psychiatry, Nursing and Midwifery Research Ethics Subcommittee (PNM RESC; Research Ethics Reference Number: PNM/13/14-125). This study will commence in spring 2016 and recruitment of HEIs started in spring 2014.

### Recruitment and consent

The participating HEIs will receive support from iConcipio to promote the study to their enrolled students via their usual communicating channels (social media, website, leaflets, and circular emails). Moreover, if the HEIs agree, SSS will be able to offer this system to students who are currently on their waiting list.

Students who are willing to participate in the study will log-in to the system and will be authenticated using university-provided credentials via single sign-on (SSO) services (e.g. Shibboleth, OAuth, LDAP lookup).^2^ They will then be directed to the information sheet. If they decide to proceed, they will access a screen listing risk statements (e.g. self-harm, substance abuse, physical harm to others, unusual sensory experiences or beliefs). At this stage, the students will not be asked to declare whether they identify with any of the statements, but they will be prompted to select either (i) the ‘proceed’ button if none of the statements applies to them or (ii) the ‘next’ button in case they need further guidance, which will lead them to a screen referring them to more appropriate services, such as their HEI student support mechanisms or mainstream helplines and help centres. If eligible (i.e. if they choose the ‘proceed’ button), the students will have access to a consent form, which they will need to sign in order to be able to register their details and use the system.

### Intervention

Following screening, students will decide whether they want to access the Library, directly choosing the techniques they are interested in or whether they want guided help, entering the Questionnaire route to identify their difficulties. Should they choose the Questionnaire route, the students will be presented with the initial screen of the system which poses the question ‘What is your hotspot today?’ allowing each student to come into the questionnaire with whatever they think the presenting problem is. The three entry points are (i) ‘It’s how I am feeling inside’, addressing psychological difficulties, (ii) ‘It’s my studies’, addressing study skills problems, and (iii) ‘It’s outside pressures’. However, the questionnaire is designed in such a way that no matter which entry point the student chooses, they will always be directed to the other points at the end of each section.

Once they choose the techniques they are interested in from the Library or upon completion of the Questionnaire, the student will be asked to rate how much their difficulties are currently affecting their life. They will then have the opportunity to name their package of techniques so that they can later find it in their personal space. At this stage, they will also decide whether they want reminders to encourage them to return to watch the videos and practice the techniques. They will then be guided to My Place where they will have access to the package with the techniques. The student will be asked to rate again at different intervals (2, 4, and 8 weeks from baseline) how much their difficulties are affecting their life after practising these techniques, and their responses will result in a graph indicating their progress over time as a self-monitoring tool. If the students give two consecutive low ratings, they will be prompted by email with information on where to seek further support. Moreover, it is stated in the description of some techniques (e.g. the two psychoeducation techniques of understanding stress and understanding low mood) that if symptoms persist for more than 2 weeks, then students should seek support elsewhere (specific referrals are again provided). Students can make notes of their thoughts regarding the techniques and their experience of them, and are given the option either to keep their thoughts private or to share them within the system’s built-in social network.

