**Methods/design:**

Two hundred and forty two students will be recruited to a within-subjects, repeated measures study conducted over 8 weeks. Self-report measures of depression and anxiety symptoms, mental wellbeing, academic self-efficacy, and everyday functioning will be collected at baseline, and then at 2, 4, and 8 weeks. During this period, students will have access to the intervention system. UK higher education institutions Bournemouth University and University of Warwick will participate in the study. Data on student satisfaction and engagement will also be collected. Study findings will help to determine the most appropriate primary outcome and the required sample size for a future trial.

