An alternative route that can be followed by students is via the Library (techniques-route). Here, students can freely browse all the available psychological and educational techniques and create a personalised package to help them improve in the areas of personal effectiveness on which they choose to focus. Both routes lead to a personal space called ‘My Place’, where students will find their package of techniques, either the package assembled for them as determined by their ‘Questionnaire’ answers or the package that they have assembled themselves in the ‘Library’.

The psychological techniques are derived from CBT. There is strong evidence supporting the effectiveness of CBT in addressing a range of emotional difficulties and associated behaviours [30–33]. Techniques considered by the expert clinical team to most likely be acceptable, feasible, and effective in the target HE population were selected for inclusion in this intervention. The educational techniques consist of the most up-to-date practical skills, extensively tested and shown to improve students’ performance [34]. They aim to help students focus their efforts better and develop successful study skills and strategies.

The techniques are presented in the form of animated videos which demonstrate evidence-based psychological and/or study skill techniques. Videos are a pioneering media for communicating evidence-based techniques to non-expert audiences, as research shows that multimedia aids learning by engaging both verbal and visual information-processing channels [35, 36].

The system has a ‘bottom-up’ design, following a symptoms- and a techniques-driven approach, to avoid the potential stigma that may be associated with applying labels to difficulties. It aims to achieve more effective and immediate results by focusing on how to ‘cope’ better with the student’s current challenges. The language, visual appearance, and feel of the system are also chosen carefully to address its target group. Overall, this online intervention is based on current scientific knowledge and best practice, and provides a mosaic comprising implicit (e.g. nudge theory, [37]) and explicit (e.g. relaxation) state-of-the-art psychological and educational strategies (e.g. how to prepare for exams).

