### Assessments

Students will be asked to complete the measures of mood (symptoms of depression and anxiety), mental wellbeing, functioning, and study skills at baseline (T0) prior to using the intervention but after giving consent, and then again at 2 weeks (T1), 4 weeks (T2), and 8 weeks (T3) from baseline. The satisfaction feedback form will be sent to participants at week 4 (T2). By collecting information at this stage, we hope that the feedback will be more reliable as students will still be practising the techniques that we wish them to appraise. Finally, after 2 months, a semi-structured interview will take place with the subsample of participants (see Table 1).

**Table 1 Tab1:** Overview of outcome measures

		Time of measurement			
Instrument	Aim	T0 baseline (pre-testing)	T1 post-test (2 weeks)	T2 follow-up (4 weeks)	Τ3 follow-up (8 weeks)
PHQ-9	Symptoms of depression	x	x	x	x
GAD-7	Symptoms of anxiety	x	x	x	x
Edinburgh-Warwick Mental Wellbeing scale	Positive mental health (mental wellbeing)	x	x	x	x
Academic self-efficacy	Academic self-efficacy	x	x	x	x
VAS	Everyday functioning	x	x	x	x
Feedback form	Engagement and satisfaction of the end-users			x	
Interview (15–20 participants)	Qualitative assessment of the experience of using the system				x
Intervention delivery	Patterns of use of the system (e.g. duration of use, total number of visits)	x	x	x	x

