### Statistical methods

#### Sample size—power calculation

This is primarily a feasibility study, so hypothesis testing of clinical outcomes is not a key part of the design. Nonetheless, to assist determination of the appropriate sample size for a definitive evaluation of this intervention, and to provide indicative values for outcome measures and change scores, a sample size calculation was conducted using the mean depression scores, standard deviation values, and change scores obtained from the evaluation of an internet depression package and comparable face-to-face psychological interventions [40, 41]. This indicates that for a paired sample *t* test, where power = 0.95 and *α* = 0.05, a total sample size of 47 is sufficient to identify differences in depression rating scores, within the range of similar published studies. For a statistical evaluation of proportional change involving a difference in caseness following intervention to 20 % from a pre-intervention case prevalence of 30 %, a total sample size of 186 will be required (where power = 0.9; *α* = 0.05). Using the more conservative estimate (186), and inflating our required number by 30 % (56) to allow for dropout, indicates that 242 participants should be recruited. Given that 873 students participated in iConcipio’s preliminary audit work, it is reasonable to expect that it will be possible to recruit a sufficiently sized sample for the feasibility study.

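### A bad week 8 rating that follows an acceptable week 4 rating cannot trigger the referral email, because the trigger needs two in a row and week 8 is the last scheduled rating (minor; participant safety only)

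*Protocol article*

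**What the plan says.** The rule and its schedule both stand in the Intervention section of the protocol article.

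- **First rating.** Once the package is settled by either route, "the student will be asked to rate how much their difficulties are currently affecting their life".
- **Later ratings.** "The student will be asked to rate again at different intervals (2, 4, and 8 weeks from baseline", that is, three more.
- **Trigger.** "If the students give two consecutive low ratings, they will be prompted by email with information on where to seek further support".
- **Other advice in the same section.** "it is stated in the description of some techniques" that a student whose symptoms last beyond 2 weeks should look for support elsewhere, with referrals given.

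The abstract describes a "repeated measures study conducted over 8 weeks". The Assessments section puts the questionnaires at baseline "and then again at 2 weeks (T1), 4 weeks (T2), and 8 weeks (T3) from baseline". Neither section adds a rating after week 8. The article describes no trigger based on a single rating and does not define which scores are low.

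**The concern.** A rule that needs two low ratings in a row uses the next rating as confirmation. At weeks 2 and 4 that is workable, because another rating is due. At week 8 nothing is due. A student who rated acceptably at week 4 and badly at week 8 has reported a worsening at the last point where the system asks, and the rule cannot respond.

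The interval before that rating is also the longest: 8 − 4 = 4 weeks, against 2 weeks for each of the two earlier intervals.

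At stake is whether a student reporting difficulty at the end of follow-up is told where to seek help. Sample size, outcome measures and analysis are not touched.

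A second weakness lies in the wording. The item asks how much difficulties affect the student's life. Read literally, a low score means little impact, and a trigger on low scores would email the students who are doing well.

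**Working it through.** There is no stated figure to reproduce. The check is to apply the rule to every possible rating history.

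**Inputs (all from Intervention).** Ratings at weeks 0, 2, 4 and 8. The email is sent at the second of two consecutive low ratings. Assumptions: low means a bad rating, only the scheduled ratings count, and the week 0 rating can be the first of a pair.

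**Enumeration.** Four ratings, each low or not low, give 2 × 2 × 2 × 2 = 16 histories. The email can first be sent at week 2 (low at 0 and 2), week 4 (low at 2 and 4) or week 8 (low at 4 and 8). Eight of the 16 end in a low week 8 rating (a dash means not low):

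| Week 0 | Week 2 | Week 4 | Week 8 | Trigger met at week 8? | First email |
|---|---|---|---|---|---|
| – | – | – | low | no | never |
| – | low | – | low | no | never |
| low | – | – | low | no | never |
| low | low | – | low | no | week 2 |
| – | – | low | low | yes | week 8 |
| low | – | low | low | yes | week 8 |
| – | low | low | low | yes | week 4 |
| low | low | low | low | yes | week 2 |

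**Result.** In the four histories with week 4 not low and week 8 low, the trigger is not met at week 8. In three of them the student gets no email at any time; in the fourth the only email came at week 2, before the improvement at week 4. When weeks 4 and 8 are both low, the trigger is met at week 8 and the rule works as written.

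**Does the baseline assumption matter?** Not for this result. The week 8 condition uses only weeks 4 and 8. If week 0 did not count, the fourth row would change from week 2 to never and the last row from week 2 to week 4; nothing else in the table would change.

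These are counts of possible histories, not shares of students. The article gives no data on how often each would occur.

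**The case against.** **Any consecutive-ratings rule leaves its last rating unconfirmed, and this one appears designed to detect persistence.** Both statements are fair. The neighbouring advice on symptoms lasting beyond 2 weeks points the same way, and a single low rating shows no persistence. This justifies waiting for confirmation at weeks 2 and 4. It does not justify it at week 8, where the confirming rating cannot arrive.

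**Other signposting exists.** That is so. There is a screen of risk statements at entry (Recruitment and consent), embedded filters and a social network watched by facilitators (MePlusMe), and the advice in some technique descriptions. A reader might infer that a student who worsens late is left with no information on support. The article does not support that. What stands is that none of these routes is described as reacting to a low week 8 rating that follows a better week 4 rating.

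**A reader might also infer that nothing responds to a low week 8 rating.** That is too broad, because the email itself does so when week 4 was low as well.

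**A reader might want delays from onset to referral, or a count of students affected.** Delays would require assuming that a rating, once low, stays low. A count would require an assumed share of students. The article supports neither.

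**The article is condensed.** The full protocol or participant materials may contain a closing message, a definition of low, or further ratings for a second package. That lowers the weight of the point. It does not remove it, because the gap follows from a rule and a schedule that the article states in full.

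**Conclusion.** The point holds as a minor, cheaply corrected gap in one referral route. Under the stated rule and schedule, a low week 8 rating after a week 4 rating that was not low cannot trigger the referral email at week 8, and no later scheduled rating can complete the pair.

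This rests on two assumptions: that low means a bad rating, and that no ratings are taken beyond those stated. Whether the baseline rating counts makes no difference. The first assumption is plausible, since an email pointing to further support makes sense only for students doing badly, but the item's literal wording runs the other way.

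The consequence is confined to participant safety. No estimate, sample size or error rate changes, and the number of students affected cannot be estimated from the documents.

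**What to change.** 1. Keep the two-consecutive-ratings rule at weeks 2 and 4.
2. At week 8, show or email the existing referral information after a single bad rating. If this is done once the week 8 questionnaires are submitted, the message cannot influence them.
3. Word the trigger by the bad end of the scale, for example as two consecutive ratings at or beyond a stated score that indicates high impact, so that it cannot be programmed in reverse.

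The cost is one automated rule and one sentence of definition before launch, using referral text that already exists, with no extra staff or visits. The downside is that some students will get a signposting message on an unconfirmed rating; the documents do not allow that number to be estimated. An unneeded message of this kind is a small burden.

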### Data collection

The system will collect data on age, gender, ethnicity (based on the UK Census 2011 categories), student status (home, EU, international), and course of study from the participating students.

### Outcome measures

#### Mood and wellbeing

Upon submission of the consent form, students will complete validated clinical measures, namely the PHQ-9 [28], a widely used 9-item self-report measure of depression symptoms, and the GAD-7 [27], a 7-item scale commonly used in clinical and research practice to assess for current symptoms of anxiety and their severity. The Edinburgh-Warwick Mental Wellbeing scale will be used to assess positive mental health (mental wellbeing). This is a 14-item scale initially validated using student populations and additionally used in national survey studies.

#### Everyday functioning

To measure everyday functioning, participants will be asked to respond to the question ‘How well are you managing now in your daily life?’ using a 5-point Likert scale, ranging from ‘extremely well’ to ‘not at all’.

#### Study skills

Self-efficacy will be assessed using an Academic Self-Efficacy scale adapted with the permission of its authors [39].

#### User satisfaction and engagement

This information will be gathered via a feedback form completed by the users, which consists ofboth open-ended and Likert-scale questions regarding the usefulness of the techniques, whether the users like how the system looks and works, fidelity (how often they used and returned to the system and whether they would prefer alternative methods of support), personal self-efficacy (whether they feel in control of their problems since using the system), and whether they presented to student support services whilst or after using the system. The system will also automatically record the following information: the average duration of MePlusMe visits, the total number of visits over the study period, the number and nature of missing answers (i.e. compliance of students to the complete filling-in of the forms), the number of students signed up for the study, and log-in patterns.

#### Acceptability of intervention

A semi-structured interview will take place face-to-face with between 15 and 20 randomly selected participants who will have expressed an interest in providing qualitative information on their experience of using MePlusMe. For inclusion in the interviews, students will have to have used the system for two full months and completed all measurements. We will also recruit students who dropped out before the full 2 months to assess their reasons for doing so. The interview will last approximately 20 min, will be recorded with consent, and will be transcribed verbatim. It will explore a number of issues, such as the elements of the system that the participants liked or did not like (quality of implementation), the ways in which they felt that the system helped them or not, how often they used the system, whether they would have prefered to consult a counsellor or to have had access to alternative methods of support instead (fidelity), and what barriers might stop them from using the system in the future.

### Assessments

Students will be asked to complete the measures of mood (symptoms of depression and anxiety), mental wellbeing, functioning, and study skills at baseline (T0) prior to using the intervention but after giving consent, and then again at 2 weeks (T1), 4 weeks (T2), and 8 weeks (T3) from baseline. The satisfaction feedback form will be sent to participants at week 4 (T2). By collecting information at this stage, we hope that the feedback will be more reliable as students will still be practising the techniques that we wish them to appraise. Finally, after 2 months, a semi-structured interview will take place with the subsample of participants (see Table 1).

**Table 1 Tab1:** Overview of outcome measures

		Time of measurement			
Instrument	Aim	T0 baseline (pre-testing)	T1 post-test (2 weeks)	T2 follow-up (4 weeks)	Τ3 follow-up (8 weeks)
PHQ-9	Symptoms of depression	x	x	x	x
GAD-7	Symptoms of anxiety	x	x	x	x
Edinburgh-Warwick Mental Wellbeing scale	Positive mental health (mental wellbeing)	x	x	x	x
Academic self-efficacy	Academic self-efficacy	x	x	x	x
VAS	Everyday functioning	x	x	x	x
Feedback form	Engagement and satisfaction of the end-users			x	
Interview (15–20 participants)	Qualitative assessment of the experience of using the system				x
Intervention delivery	Patterns of use of the system (e.g. duration of use, total number of visits)	x	x	x	x

### Statistical methods

#### Sample size—power calculation

This is primarily a feasibility study, so hypothesis testing of clinical outcomes is not a key part of the design. Nonetheless, to assist determination of the appropriate sample size for a definitive evaluation of this intervention, and to provide indicative values for outcome measures and change scores, a sample size calculation was conducted using the mean depression scores, standard deviation values, and change scores obtained from the evaluation of an internet depression package and comparable face-to-face psychological interventions [40, 41]. This indicates that for a paired sample *t* test, where power = 0.95 and *α* = 0.05, a total sample size of 47 is sufficient to identify differences in depression rating scores, within the range of similar published studies. For a statistical evaluation of proportional change involving a difference in caseness following intervention to 20 % from a pre-intervention case prevalence of 30 %, a total sample size of 186 will be required (where power = 0.9; *α* = 0.05). Using the more conservative estimate (186), and inflating our required number by 30 % (56) to allow for dropout, indicates that 242 participants should be recruited. Given that 873 students participated in iConcipio’s preliminary audit work, it is reasonable to expect that it will be possible to recruit a sufficiently sized sample for the feasibility study.

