#### Data analysis

This being a feasibility study, descriptive findings concerning recruitment numbers, completions, drop-outs, and summary estimates of outcome measures at baseline and follow-up focussing on the dropout rate at each time point will be explored. We will also conduct exploratory analyses of the pre-post effect of the intervention using the data from participants who have completed the programme. To examine differences before and after using MePlusMe, we will conduct a 4 × 4 repeated measures ANOVA with time (four time-points) and the four assessments (PHQ-9, GAD-7, Edinburgh-Warwick Mental Wellbeing scale, Academic Self-Efficacy scale, and VAS ratings) as the within-subject variables. Effect sizes will be presented as Cohen’s *d.* This will enable determination of the outcome measure mean, standard deviation and variance, and change, which will be essential for designing an appropriately powered trial.

Qualitative data from the feedback form will be analysed using content analysis. Interviews and analyses will be performed concurrently using the principles of constant comparison [42] and thematic analysis [43]. At least two researchers will independently code the first interview and agree on descriptive codes. These codes, and where appropriate further new codes, will be applied to subsequent transcripts. Consistency in coding will be checked within the research team. Descriptive codes will be collated into themes and a preliminary explanatory framework devised. This will be used as the basis for coding and for informing future interviews. The robustness of themes will be tested by examining differences and similarities between coded data.

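### The 30% dropout allowance is added to the required 186, so a target of 242 preserves 186 completers only up to 23.1% dropout

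*Protocol article*

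**What the plan says.** All the figures are in the protocol article, under Sample size—power calculation. The comparison that drives the size is "a difference in caseness following intervention to 20 % from a pre-intervention case prevalence of 30" per cent, for which "a total sample size of 186 will be required (where power = 0.9; *α* = 0.05"). The article treats this as the more conservative of two calculations; the other gives 47 for a paired *t* test on depression scores at power 0.95.

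The step to the recruitment target is described as "inflating our required number by 30 % (56) to allow for dropout", and the result is stated in the words "to allow for dropout, indicates that 242 participants should be recruited". The Abstract (Methods/design) repeats the result: "Two hundred and forty two students will be recruited". No attrition or retention rate is given anywhere in the article.

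Two other statements set the context. Under Data analysis, the exploratory pre-post analyses are to be done "using the data from participants who have completed the programme". The sample size section opens by saying that "hypothesis testing of clinical outcomes is not a key part of the design".

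**The concern.** The purpose given for the extra 56 is dropout, and dropout removes a share of the people recruited. Adding a share of the number needed at the end is a different operation, and it always gives a smaller target than the loss rate of the same size requires. A reader who sees 30% next to the word dropout will take it that the study can lose 30% of its participants and still have the 186 it calls required. It cannot.

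Three features make this relevant here.

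- The pre-post analysis uses completers, so each person lost reduces it directly.
- The dropout rate at each time point is one of the quantities the study sets out to describe. An observed rate between 23.1% and 30% would look as if it fell within the allowance, while the number of completers was already below 186.
- The calculation is presented as helping to size a definitive evaluation, so the method is worth getting right before then.

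**Working it through.** **Inputs, all from Sample size—power calculation:** required number 186; allowance 30% of that number, given as 56; target 242; caseness 30% before and 20% after; power 0.90; α 0.05, sidedness not stated. The 186 is taken as given.

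**1. Reproducing the article's figure, n × (1 + d).**
186 × 0.30 = 55.8, rounded to 56. 186 + 56 = 242. This matches exactly, so the method is not in doubt.

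**2. Dropout that 242 covers.**
1 − 186/242 = 56/242 = 0.231, or 23.1%.

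**3. Completers if 30% of recruits are lost.**
242 × 0.70 = 169.4, about 169. Shortfall: 186 − 169 = 17, and 17/186 = 9%.

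**4. Target that matches a 30% loss, n/(1 − d).**
186/0.70 = 265.7, so 266, which is 24 more than 242. Check: 266 × 0.70 = 186.2.

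**5. Illustrative power at 169.** A comparison of caseness in the same people before and after is a paired comparison of proportions, so I use the normal approximation to the McNemar test. It needs the proportion of people whose case status changes in either direction (the discordance, ψ), which the article does not give. With difference δ = 0.30 − 0.20 = 0.10 and a two-sided test:

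n = [(1.960√ψ + 1.282√(ψ − δ²)) / δ]²

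Setting n = 186 gives ψ = 0.181. Check: 1.960 × 0.4254 + 1.282 × 0.4135 = 1.364; (1.364/0.10)² = 186.

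Power = Φ[(δ√n − 1.960√ψ) / √(ψ − δ²)]

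At n = 169: (0.10 × 13 − 0.834)/0.4135 = 1.127, so power is 0.87, against 0.90 at 186.

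**6. Sensitivity to the assumption.** The same formula, two-sided, with ψ running from its minimum (0.10, all change in one direction) to its value if the two assessments were independent (0.30 × 0.80 + 0.70 × 0.20 = 0.38):

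| ψ | Power at 186 | Power at 169 |
|---|---|---|
| 0.10 | 0.99 | 0.99 |
| 0.14 | 0.96 | 0.94 |
| 0.181 | 0.90 | 0.87 |
| 0.22 | 0.83 | 0.80 |
| 0.30 | 0.71 | 0.66 |
| 0.38 | 0.60 | 0.56 |

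Only the row at 0.181 agrees with the article's 186 at 0.90. If the test was one-sided (1.645 in place of 1.960), the discordance that gives 186 is 0.222, and power at 169 is again 0.87. As a cross-check by a different route, a two-sided one-sample test of 20% against a fixed 30% gives 0.88 at 186 and 0.84 at 169. Across these, going from 186 to 169 costs at most about 4 percentage points.

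**The case against.** The strongest reply is that the article contains no arithmetic error. It says that the required number is what is being inflated, it spells out the increment of 56, and the sum is right. It nowhere says that 30% of recruits are expected to leave. On that reading the 30% is an inflation factor, and nothing has been promised about a 30% loss.

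This stands in part. A reader might infer that 242 will leave only 169 completers, or that the plan fails to reach its stated power, as plain facts. The article does not support either without a condition: both follow only if 30% is the proportion of recruits expected to be lost. What follows without any condition is that 242 covers a loss of 23.1% and no more. The reply does not remove the problem, because dropout is the only reason given for the 30%. Either the intended loss is 30% and the target does not match it, or the tolerated loss is 23.1% and the sentence does not say so.

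A second reply is that little depends on it. Hypothesis testing is not central, the analysis described for the clinical scores is a repeated measures ANOVA with Cohen's *d*, and no caseness test appears under Data analysis. For the depression score the article's own requirement is 47, and 169 is about 3.6 times that (169/47). This is right and limits the severity.

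A third is that the effect on the randomised trial is speculative. A reader might infer that the same shortfall will pass into that trial. The article does not say that the inflation method will be reused, and the dropout observed in this study would be the natural input. The point for the trial is therefore advice on method.

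**Conclusion.** The point holds in conditional form. Without further assumption, the stated allowance keeps 186 completers only up to 23.1% dropout. If 30% of recruits are expected to drop out, 242 gives about 169 completers, 17 (9%) fewer than the number described as required, and the 0.90 power for the caseness comparison is not met. The figure of about 0.87 is an illustration: it rests on a McNemar test and on a discordance of about 0.18 chosen so that 186 gives 0.90.

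Severity is minor to moderate. The sentence misdescribes what a headline figure covers, but the loss of power is small and the feasibility aims do not depend on it. The finding does not show that 242 is too few for this study.

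**What to change.** Keep 242 and correct the sentence in Sample size—power calculation. State the expected dropout rate and use one of two wordings:

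- 242 recruited allows for about 23% dropout while keeping 186 completers; or
- 242 recruited with 30% dropout gives about 169 completers, with the power restated for 169 and the test, sidedness and discordance behind it given.

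Use n/(1 − d) when the future randomised trial is sized, with d taken from the dropout observed here.

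For information only, the recruitment figure that matches a 30% loss is 266. Enrolling 24 more is not needed to resolve the point.

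The cost is one sentence and a slightly less favourable stated dropout tolerance or power. The Abstract gives only the recruitment number, so it needs no change if 242 stands.
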